## Abstract

**Background:**

The prevalence of osteoarthritis and knee osteoarthritis in the Spanish population is estimated at 17% and 10.2%, respectively. The clinical guidelines concur that the first line treatment for knee osteoarthritis should be non-pharmacological and include weight loss, physical activity and self-management of pain. Health Coaching has been defined as an intervention that facilitates the achievement of health improvement goals, the reduction of unhealthy lifestyles, the improvement of self-management for chronic conditions and quality of life enhancement.

The aim of this study is to analyze the effectiveness, cost-effectiveness and cost-utility of a health coaching intervention on quality of life, pain, overweight and physical activity in patients from 18 primary care centres of Barcelona with knee osteoarthritis.

**Methods/Design:**

Methodology from the Medical Research Council on developing complex interventions. **Phase 1:** Intervention modelling and operationalization through a qualitative, socioconstructivist study using theoretical sampling with 10 in-depth interviews to patients with knee osteoarthritis and 4 discussion groups of 8–12 primary care professionals, evaluated using a sociological discourse analysis. **Phase 2:** Effectiveness, cost-effectiveness and cost-utility study with a community-based randomized clinical trial. *Participants*: 360 patients with knee osteoarthritis (180 in each group). *Randomization unit*: Primary Care Centre. *Intervention Group*: will receive standard care plus 20-hour health coaching and follow-up sessions. *Control Group*: will receive standard care. *Main Outcome Variable*: quality of life as measured by the WOMAC index. *Data Analyses*: will include standardized response mean and multilevel analysis of repeated measures. *Economic analysis:* based on cost-effectiveness and cost-utility measures. **Phase 3:** Evaluation of the intervention programme with a qualitative study. Methodology as in Phase 1.

**Discussion:**

If the analyses show the cost-effectiveness and cost-utility of the intervention the results can be incorporated into the clinical guidelines for the management of knee osteoarthritis in primary care.

**Trial registration:**

ISRCTN57405925. Registred 20 June 2014.

## Background

Knee osteoarthritis (KO) is a chronic condition characterized by the progressive deterioration of articular cartilage and subchondral bone. KO has multiple causes that produce similar biological, morphological and clinical symptoms. The major clinical features of KO are pain with physical activity, restricted ability to walk and stand, and a progressive deformation of the knee joint. KO is frequently accompanied by obesity/overweight (90%), hypertension (40%), depression (30%) and diabetes (15%). These comorbidities contribute to a decreased quality of life [1].

Globally, it is estimated that 24% of the general adult population suffers from osteoarthritis. Symptomatic osteoarthritis affects 9.6% men and 18% women 60 years or older and its prevalence increases with age, up to 80% in people over 65 years of age in high-income countries. The increase in life expectancy will raise the number of patients affected by osteoarthritis. In the USA, 19% of the general population has a radiographic diagnosis of KO and 7% present knee symptoms. The prevalence of osteoarthritis is 17% and 16.6% in the general Spanish and Catalan populations, respectively, while the prevalence of knee osteoarthritis is 10.2% [2].

Osteoarthritis is responsible for the loss of 1.9 Quality Adjusted Life Years (QALYs) in people between 50 and 84 years of age [3]. The loss in obese individuals can reach 3.5 QALYs. According to Hunter [1], mortality rates in patients with osteoarthritis are higher compared with the general population (Standardized Mortality Ratio 1.55: 95% CI: 1.41-1.79). Osteoarthritis generates high costs (€1,502 per patient yearly), most of which (86%) are direct costs derived from medical care and dependency, such as help at home and at work. Indirect costs refer to loss of productivity and include help at home for affected housewives. It is, therefore, a condition with a high social impact [4]. Studies carried out in Norway and Spain show that the national cost for osteoarthritis can reach €3,528 million [5] and €4,700 million [4], respectively.

Clinical guidelines for osteoarthritis recommend a non-pharmacological first-line treatment for patients with osteoarthritis which should include weight loss, healthy eating habits, physical activity, self-management of pain, information-education and orthoses [6]. In particular, they recommend the education of patients even if the current evidence remains inconclusive [2,7,8]. Indeed, non-pharmacological recommendations frequently lack precision regarding contents, duration, intensity and frequency and might result in the suboptimal care afforded to osteoarthritis patients observed in several studies [2].

A great diversity of educational interventions takes place in primary care. Most of them are based on brief advice as recommended in the clinical guidelines and in primary care journals. Accordingly, the recommendations related to osteoarthritis within the “*Health Plan for Rheumatological and Musculoskeletal Conditions*” [9] aim to encourage all measures that enhance quality of life through health promotion, prevention and self-care, with a particular emphasis on modifiable risk factors such as obesity, optimal use of orthoses and exercise. The recommendations also underscore the need to minimize variability in clinical outcomes by improving the efficiency of diagnosis and therapy through a specific training of primary care doctors and nurses.

Self-management education programmes targeting patient education and behaviour modification were not more effective than usual clinical practice, information or other alternative therapies according to Kroon et al. [10]. However, the authors conclude that clinical trials that assess other self-management educational programmes for osteoarthritis might be warranted. Our study is based on the behaviour change framework [11], which takes into account Argyris’ theory [12] and the links between change processes and determinants of behaviour such as Prochaska’s stages of change [13].

Some interventions that focus on the promotion of healthy habits include two essential aspects: complexity and use of health coaching. The complex, multimodal and multidisciplinary design results in an intervention better suited to its context which therefore achieves better results and greater sustainability. The Medical Research Council has established a methodology for complex interventions that consists of several phases that can be repeatedly implemented and that use qualitative and quantitative methods [14].

Health Coaching originates within the conceptual framework of behaviour change and specifically in Argyris’ Action Theory [12]. Health Coaching is a behavioural intervention to facilitate patients adopt and sustain their own health related goals, change attitudes, decrease unhealthy habits, improve the management of chronic conditions and generally increase health related quality of life [15].

Health coaching can improve treatment adherence in chronic patients [16], is effective towards glycemic control and diabetes [17], oncological pain, self-management of pain [18], moderate weight loss and the improvement of healthy habits that result in weight loss and the promotion of a healthy diet and physical activity [19].

Several research protocols currently include coaching-based interventions to promote healthy lifestyles in elderly people at moderate risk of suffering from cardiovascular conditions, diabetes and depression, and also for patients on low incomes and poorly-controlled diabetes, hypertension or hyperlipidemia. Coaching is conducted by a medical assistant as a health coach and with telephone support [20]. These interventions can be carried out by different health professionals and even by people suffering from the same condition (peer health coaching); in this last instance, these patients must receive coaching training. In the study of Thom and colleagues, the researchers themselves were the coaches [17], whereas in Thomas et al. the trainer was a psychologist [18].

No studies on the application of health coaching to osteoarthritis of the knee have been published to date. Moreover and to our knowledge, clinical guidelines for osteoarthritis of the knee are not implemented in primary care when the treatment of choice is non-pharmacological. Since most guidelines recommend non-pharmacological treatment for pain self-management, weight loss and increased physical activity [1,2,7,8], our study aims to provide evidence on the effectiveness of health coaching on KO by developing a complex intervention that will focus on the patient and will encourage participation, to promote the patients’ knowledge of their condition and to facilitate the achievement of their therapeutic goals in accordance with their own resources. Telephone support will ensure that the patient manages the osteoarthritis with the highest possible independence and quality of life [7].

This study aims to implement a flexible, complex intervention adapted to the people with osteoarthritis and that is feasible, effective and sustainable in primary care centres. The intervention aims to promote healthy behaviour, decrease unhealthy habits and improve quality of life and the control of osteoarthritis. Ultimately, it should encourage a healthy and active ageing process by preventing also other prevalent diseases. Indeed, health promotion behaviours contribute to a less dependent and a more satisfactory older age.

In line with the WHO recommendations for active ageing [21], to remain socially and mentally active the coaching intervention of our study will encourage the use of the patient’s own strategies to: 1. promote healthy habits and physical exercise to reduce risk factors of disease; 2. promote cognitive vitality; 3. promote a positive approach to problems and emotions; 4. promote social participation [15].

If the study proves the cost-effectiveness and cost-utility of the intervention, a local adaptation could be incorporated into the clinical guidelines and implemented in primary care centres. In our study the health coach is a psychologist who will also train primary care professionals to integrate coaching in everyday clinical practice.

## Objectives

### Main objective

To analyze effectiveness, cost-effectiveness and cost-utility of an intervention based on health coaching and telephone support on quality of life, pain, overweight/obesity and physical activity in patients from Primary Health Care Centres (PHCC) of the Barcelona province suffering from osteoarthritis of the knee, compared with usual care.

### Secondary objectives

To identify the barriers and facilitators of an intervention based on health coaching with a qualitative study that includes individual interviews to patients suffering from osteoarthritis and group interviews with primary care professionals, with the aim to design an intervention adapted to primary care patients and professionals. Based on the experience and opinion of participating patients and professionals, to evaluate the acceptability and feasibility of the intervention.

## Methods/Design

The Medical Research Council has established a methodology for this type of complex interventions that consists in several phases that can be repeatedly implemented and that use qualitative and quantitative methods [14]. Our study comprises three phases:

### Phase 1: modeling and operationalization of the intervention

#### Qualitative study

The aim of the phase is to identify the key factors that can influence the development of the intervention. It will identify the barriers and facilitators of the health coaching intervention on KO for patients and health professionals. The participants in this study will be adults with osteoarthritis of the knee and the primary care professionals responsible for treating this condition. In this phase we will specify the different components of the intervention and determine the factors related to patients, professionals and other that facilitate or restrict the intervention (acceptability, adequacy, feasibility, integration within other programmes, location, schedule and duration).

The qualitative study will use a socioconstructivist perspective and theoretical sampling. Ten semi-structured interviews will be conducted with patients suffering from osteoarthritis to identify their beliefs, knowledge and perceptions on the components and conceptual model of the intervention.

We aim to reach discourse saturation through interviews to men and women of different ages and literacy levels. The four discussion groups will include 8–12 primary care professionals working with patients with osteoarthritis to identify their attitudes, opinions, motivation and to verify their competence on coaching, knee osteoarthritis and information and communication technology (ICT) [22].

#### Operationalization of the intervention

The results of the qualitative study will provide information towards the operationalization of the intervention, so that it adapts to the needs and reality of the PHCCs patients and professionals. An informative session will be held in the participating PHCCs to explain the results of the qualitative study; the objectives and characteristics of the study and the intervention and recruitment strategies will be explained to the professionals. Recruitment will be coordinated by a research team member together with the designated professional of the PHCC.

#### Analysis of qualitative data

A sociological discourse analysis based on Hodges’ criteria will be carried out [23]. Masked, anonymized literal transcriptions of the recorded sessions will be produced. After consecutive readings of the transcriptions and the formulation of preanalytical intuitions, we will analyse the social status of patients and professionals. Next, we will analyse the discursive fractions, determined by their positioning in relation to the subject discussed (discursive positioning). Then, we will generate a global interpretation of the text in relation to the objectives of the research to organize the whole discourse and to link it to the context (symbolic configuration). Next, we will carry out the internalist analysis of the text looking for semantic attractors and associative chains (semantic configuration) with the assistance of the Atlas-Ti programme. Finally, the discourse will be reconstructed and the analysis will be triangulated between the members of the research team.

#### Applicability of results

The results of Phase 1 will provide information on barriers and facilitators for the design of a flexible intervention adapted to the needs of primary care patients and professionals.

### Phase 2: study of effectiveness, cost-effectiveness and cost-utility

#### Design

Cluster randomized clinical trial. The PHCC will be the unit of randomization.

#### Study setting

18 PHCCs of the province of Barcelona that agree to participate (9 PHCCs per study group). The PHCCs will be randomized into the complex, multidisciplinary intervention (health coaching with telephone support + usual care in PC) or the control group (usual care in PC).

#### Participants

360 participants, 180 per group.

#### Inclusion criteria

Level 1. Inclusion criteria to be determined by the physician: primary care patients with clinical and radiological diagnosis of knee osteoarthritis in the Kellgren-Lawrence stages 1–3 [24]; to be able to read and write; to have a mobile phone; to be able to go to the PHCC; and to agree to participate. Level 2. Inclusion criteria to be determined by the psychologist: patients that deliver the “commitment folder” within the period agreed. This report will measure the stage of change [13] of the patient [11].

#### Exclusion criteria

The following patients will be excluded: patients with knee osteoarthritis in the Kellgren-Lawrence stages 0 and 4; patients with rheumatoid arthritis, fibromyalgia and other systemic rheumatological conditions; patients on a waiting list for orthoses; patients admitted during the past three months for cardiovascular diseases; patients suffering from Parkinson disease, Paget’s disease, cognitive deterioration, metastatic cancer, severe mental diseases and personality disorders; women pregnant or planning a pregnancy.

### Intervention design

#### Intervention Group (IG)

The intervention programme is divided in two phases: the intensive phase, which lasts 20 hours distributed along one month (Table 1); and the follow up phase. The results of Phase 1 of the current study will determine the periodicity and other components (described in the phase 1) of the intensive phase.

**Table 1 Tab1:** **Intervention programme: intensive phase**

**Duration**	**Goals**	**Contents**	**Components**
2 hours	• Presentation	**About Health Coaching:**	1. Motivation Techniques
	• Sharing and Explaining Concepts	1. What is health coaching?	2. Group Development Techniques
	• Motivate participants	2. Who can benefit ?	3. Evidence-based Information
	• Agree conditions of intervention	3. The health coaching process	
		a. General outline	
		b. Confidentiality (with reference to ethical code)	
		4. What is it useful for?	
		**Knee Osteoarthritis:**	
		1. What is it?	
		2. How can it be treated?	
		Tasks	
		Agreement on conditions of intervention	
12 hours	• Increase physical activity	1. Review of Tasks	1. Motivation Techniques
	*Increase healthy diet	2. Goal Setting	2. Group Development Techniques
	*Increase self-management of pain techniques and strategies	3. Analyze current situation	3. Evidence-based Information
		4. Options	
		5. Action Plan	
		6. Creation of guideline for self-monitoring (goal achievement process)	
		7. Creation of guideline for self-evaluation of action plan (goal achievement)	
6 hours	• Follow-up of Action Plan and Evaluation of Results	1. Provide the patient with strategies and techniques to follow the action plan through	
		2. Review Action Plan	
		3. Review Evaluation of Results	
		4. Evaluation of Results	
		5. Prevention of Relapse	
**Intervention Programme-follow-up phase**			
**Frequency**	**Goals**	**Contents**	**Components**
Once monthly	Maintain Motivation Weight Control	Positive Reinforcement Empower and Train Laser Questions	1. Motivation Techniques
			2. Group Development Techniques
			3. Evidence-based Information

A psychologist coach is in charge of the intensive phase, which includes motivational, coaching psychology and group development techniques, and evidence based information. Four pillars (mindful presence, authentic communication, self-awareness and safe place) [25] and seven elements that determine behaviour change (self-regulation, skills, self-efficacy, expected outcome, intention, context and regulations) [11] are the cornerstone of health coaching.

#### Allocation of time

Two hours for the following objectives: presentation of the programme, merge the prior knowledge of participants, motivate them and agree on the conditions of the intervention. The following aspects will be discussed: what is health coaching psychology, who can benefit from health coaching, how it works, how it is implemented, confidentiality and aims of the intervention. The treatment and causes of knee osteoarthritis will be also discussed.Twelve hours for the following objectives: scale up physical activity, improve nutrition and increase strategies for the self-management of pain. The following aspects will be discussed: definition of goals, analysis of the current situation, options, action plan and production of individual guidelines for the self-assessment of goal attainment and for the self-assessment of the action plan.Six hours for the following objectives: follow up of the action plan and assessment of results. The following aspects will be discussed: techniques and strategies to follow through the action plan, review of the action plan, review of the assessment of results, assessment of results and prevention of relapse.

The follow up will take place in the primary care centre of the participant, with their own GP and nurse. The nurse and GP will receive training to sustain motivation and weight control. Specifically, they will be trained on positive feedback, patient empowerment and laser questions with motivation and coaching psychology techniques and evidence based information. The pillars and elements of behaviour change will be the same as in the intensive phase. These individual sessions will be conducted monthly and they will last as much as any other follow up visit.

Compliance in relation to the group sessions will be assessed by registering the number of group sessions attended. To ensure patients’ adherence to the group sessions, they will be able to choose between morning or afternoon sessions. One week prior to the group session, they will receive a phone call to remind them the date, time and place of the session and on the day before they will receive an SMS reminder.

#### Control Group (CG)

The participants allocated to the CG will follow usual care based on recommendations and brief advice by the primary care physician and/or nurse [1,7,8], as recommended by the clinical guidelines. These recommendations to control pain, maintain functionality and prevent progression of disease include: weight control, correct body posture, thermotherapy, adherence to treatment, physical exercise, rest and orthosis.

#### Recruitment

In addition to considering the results of Phase 1, recruitment will take place through: 1. Patients who go to the doctor for knee osteoarthritis or other health problems; 2. People with a diagnosis of knee osteoarthritis in the electronic medical records; 3. Information posters in the waiting rooms of the PHCCs. If the patient agrees to participate, the physician and/or nurse will give him/her a “commitment folder” and the informed consent form. The patient must study the documentation and bring it back to the PHCC within two weeks (See Figure 1).

**Figure 1 Fig1:**
[figure not shown]
**Flow chart (Phase 2).** Notes: OK = Osteoarthritis Knee; GP = general practitioner; PHCC = Primary Health Care Centres.

#### Outcomes

The main outcome variable is quality of life as measured by the WOMAC index [26]. Secondary outcomes are: pain [27], weight, physical activity [28] and nutrition [29].

#### Other variables

The main independent variable is the intervention arm: coaching group intervention or usual care.

Socio-demographic, clinical and cost variables will be recorded. Table 2 shows the study variables and the measurement instruments, validated in Spanish and for primary care.

**Table 2 Tab2:** **Data collection, information sources and follow-up**

**Variables**					**Data collection**				
					**Baseline**	***Follow up from recruitment**			
**Clinical dependent variables**	**Measurement instrument**	**Type of response**	**Scoring (total and per item)**	**Range**	**Before intensive phase**	**After intensive phase**	**3 months**	**6 months**	**12 months**
Qual ity of Life	WOMAC (Batl le, 1999)	Likert (0=none to 4=very much)	TOTAL=24 17= functional l imitation 5=pain 2= sti ffness	0-96	X	X	X	X	X
Pain	ICOAP (Mai l lafert, 2009)	Likert (0=none to 4=very much)	TOTAL = 11 5= constant pain 6= intermittent pain	0-44	X	X	X	X	X
Weight (in Kg.)*	Scale at the PCC	Quantitative (kg.)	-	0 - ∞	X	X	X	X	X
Physical Activity	IPAQ (Puig, 2012)	Duration + Frequency of Moderate to Intense	TOTAL= 7	0 - 3000 MET	X	X	X	X	X
Physical Activity*	Pedometer	Quantitative	-	0 - ∞					
Nutrition	PREDIMED (Mediterranean Diet Adherence Questionnaire	Dichotomous (YES= 1 point NO= 0 points)	TOTAL = 14 12= frequency of consumption of foods 2= Mediterranean food habits	0-14	X	X	X	X	X
Other Variables									
Socio-demographic									
Age, gender, educational level, work status, number of children	Ad-hoc Questionnaire	Nominal	-	-	-	X			
Clinical				-					
Drug Prescription	Ad-hoc Questionnaire	Nominal	1	-	X	X	X	X	X
Diagnostic tests	Ad-hoc Questionnaire	Nominal	1	-	X				X
Waist Circumference	Ad-hoc Questionnaire	Quantitative (cm.)	1	-	X	X	X	X	X
Height	Ad-hoc Questionnaire	Quantitative (cm.)	1	-	X				X
Comorbidities	Ad-hoc Questionnaire	Nominal	1	-	X	X	X	X	X
Duration of Disease in Years	Ad-hoc Questionnaire	Quantitative (years)	1	-	X				
Duration Knee Osteoarthritis in	Ad-hoc Questionnaire	Quantitative (years)	1	-	X				
Costs-related			-						
Direct Medical			-						
Cost of coaching in osteoarthrosis	Ad-hoc Questionnaire	Quantitative (euros)	-	-	X	X	X	X	X
Cost of visits to the GP	Ad-hoc Questionnaire	Quantitative (euros)	-	-	X	X	X	X	X
Cost of visits to the nurse	Ad-hoc Questionnaire	Quantitative (euros)	-	-	X	X	X	X	X
Cost of visits to the physiotherapist	Ad-hoc Questionnaire	Quantitative (euros)	-	-	X	X	X	X	X
Cost of visits to special ist MD	Ad-hoc Questionnaire	Quantitative (euros)	-	-	X	X	X	X	X
Cost of Medical Tests	Ad-hoc Questionnaire	Quantitative (euros)	-	-	X	X	X	X	X
Cost of Pharmacological	Ad-hoc Questionnaire	Quantitative (euros)	-	-	X	X	X	X	X
Operating Costs of the PCC	Ad-hoc Questionnaire	Quantitative (euros)	-	-	X	X	X	X	X
Cost of Disposable Medical Equipment	Ad-hoc Questionnaire	Quantitative (euros)	-	-	X	X	X	X	X
Cost of transport (ambulance)	Ad-hoc Questionnaire	Quantitative (euros)	-		X	X	X	X	X
Cost of Home Assistance	Ad-hoc Questionnaire	Quantitative (euros)	-		X	X	X	X	X
Indirect Medical			-						
Costs due to loss of productivity (days of sick leave)	Ad-hoc Questionnaire	Uantitative (euro	-		X	X	X	X	X

* Monthly.

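### The cost list counts lost productivity only as sick leave and transport only as ambulance, so working time and own travel used by the coaching programme stay out of the incremental cost

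*Protocol article*

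**What the plan says.** The cost-related part of Table 2 is an itemised list. Under direct medical costs it has eleven lines: coaching, four kinds of professional visit, tests, drugs, centre operating costs, disposables, transport and home assistance. The transport line reads "Cost of transport (ambulance" and the programme itself is one line, "Cost of coaching in osteoarthrosis". Under indirect costs there is a single line: "Costs due to loss of productivity (days of sick leave".

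The section on the intervention group describes "the intensive phase, which lasts 20 hours distributed along one month". The section on allocation of time adds that, for the group sessions, patients "they will be able to choose between morning or afternoon sessions", and that attendance at these sessions is registered. Of the follow-up phase it says: "These individual sessions will be conducted monthly and they will last as much as any other follow up visit". Controls "will follow usual care based on recommendations and brief advice by the primary care physician and/or nurse".

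The section on the economic evaluation refers to Table 2 for costs. It sets a 12-month horizon and puts the between-group difference in mean costs in the numerator of both the cost-effectiveness and the cost-utility ratio. It plans a sensitivity analysis on discount rates and costs. It states no perspective.

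**The concern.** Including sick leave brings productivity into the total. It is the productivity lost to illness. The productivity used up by attending the programme has no line, and neither does the patient's own travel. The 20 hours of sessions arise only in the intervention arm, so leaving out what they cost patients lowers that arm's mean cost and not the control arm's.

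The incremental cost feeds both ratios and the acceptability curves. Cost-effectiveness and cost-utility belong to the main objective, and the abstract and discussion make possible adoption into clinical guidelines depend on them. An error of known direction in that numerator is worth removing, even if it proves small.

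**Working it through.** The plan states no incremental cost, so there is no figure of its own to reproduce. The sample size does not depend on this point.

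**Step 1: set the programme's demands on patients against the cost list.**

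| Demand on the patient | Arm | Line in Table 2 that captures it |
|---|---|---|
| 20 hours of group sessions: working time | Intervention only | None; a part-day absence is not a day of sick leave |
| Trips to the sessions | Intervention only | None; only ambulance transport is listed |
| Monthly visits: staff cost | Net extra over usual visits | GP and nurse visit lines |
| Monthly visits: working time and trips | Net extra over usual visits | None |

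The coaching line sits under direct medical costs, and nothing shows that it covers patient time or travel. Varying the listed costs in a sensitivity analysis does not add an unlisted one.

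**Step 2: benchmark from the Background section.** It gives a yearly cost of "1,502 per patient yearly), most of which (86%) are direct costs". The indirect share is 100% - 86% = 14%, and 0.14 x 1,502 = 210 euros per patient-year, averaged over all patients whether or not they work.

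**Step 3: working time for the 20 hours.** Average cost per intervention patient = (hours / 8) x share in work x value of a working day. The 20 hours come from the protocol. The eight-hour day, the share in work (20-40%) and the daily value (60-120 euros) are assumptions. Full attendance, and sessions that fall wholly in working hours for those who work, are also assumed.

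- 20 / 8 = 2.5 days.
- Per working patient: 2.5 x 60 = 150 euros to 2.5 x 120 = 300 euros.
- Averaged over the arm: 0.2 x 150 = 30 euros to 0.4 x 300 = 120 euros.
- Against the benchmark: 30 / 210 = 14% to 120 / 210 = 57%.
- Against the whole yearly cost: 30 / 1,502 = 2% to 120 / 1,502 = 8%.
- If nobody works, the figure is 0.

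**Step 4: monthly visits.** If follow-up visits run for the remaining 11 months of the horizon, each takes one hour and all are additional (assumptions), the extra is 11 / 8 = 1.375 days. That gives 0.2 x 1.375 x 60 = 16.5 euros to 0.4 x 1.375 x 120 = 66 euros. If the monthly visits only replace ordinary ones, it is 0.

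**Step 5: own travel.** The number of sessions and the price of a trip are not given. Assume 4 to 10 sessions and 2 to 8 euros per trip.

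- No net extra visits: 4 x 2 = 8 euros to 10 x 8 = 80 euros.
- All 11 visits additional: (4 + 11) x 2 = 30 euros to (10 + 11) x 8 = 168 euros.

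**The case against.** The strongest reply is that this is a condensed article. The perspective, the valuation rules and the content of the questionnaire may be set out elsewhere, and the coaching line is undefined. A narrower perspective could properly leave patient time out. This stands in part: how session hours are valued can still be fixed in an analysis plan, because attendance, visits and work status are already collected. It does not dispose of the point. The article gives an itemised list, not silence. Own travel has no item and cannot be analysed later if it is never asked. Under a narrower perspective the sick-leave line would not belong in the main total.

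A reader might infer several stronger things that the document does not support:

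- *That the list credits coaching with sick-leave savings.* Sick leave is measured in both arms and favours coaching only if it falls.
- *That the whole burden falls on one arm.* This is true of the 20 hours. Follow-up visits are with the patient's own GP and nurse and last as long as ordinary ones, controls also see these professionals, and the discussion notes that these patients visit often. Only net extra visits count.
- *That the home-assistance line shows a view wider than the payer's.* Table 2 files it under direct medical costs, and the Background section counts help at home among direct costs of dependency. Only the sick-leave line carries the argument.
- *That the omitted time is as large as the whole indirect cost.* This sets 150-300 euros per working patient against 210 euros averaged over all patients. The like-for-like figure is the arm average.

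It is also fair that the choice of morning or afternoon lets some workers avoid working hours, and that the discussion expects most participants to be over 60. Both push the working-time figure down.

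**Conclusion.** The point holds as an inconsistency in the cost list. Followed as written, total costs include productivity lost to illness but not working time or own travel spent on the programme. The omitted session cost cannot be negative and arises only in the intervention arm, so the incremental cost of coaching is understated.

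The size is not set by the document. Under the stated assumptions, session time is about 30-120 euros per intervention patient on average, or 14-57% of the roughly 210 euros benchmark. It could be near zero if few participants work or if sessions avoid working hours. Net extra visits and own travel add to it. This is a bias of known direction and uncertain size. It does not show that the conclusion on cost-effectiveness would change.

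**What to change.** State the perspective of the economic evaluation and make the base case follow it, in one of two ways:

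- **Health-payer base case.** Leave sick-leave productivity out of the main total and report it in a secondary analysis.
- **Base case with productivity.** Keep sick leave and add, in both arms, working time lost to sessions and visits, valued at the same daily rate as sick leave, plus own travel. Hours come from the attendance register, the visit counts and the recorded work status; travel needs one added question. Recording both arms ensures that only net extra visits count.

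Report the view not chosen as a sensitivity analysis, and say what the coaching line contains.

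The cost is some wording, one question and use of a register that is already planned. The stated cost of coaching may look somewhat less favourable. Sample size, outcomes and care are unchanged.
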